**Subgroup analyses**

We will stratify all analyses using the results of the prediction modeling as this is intended to affect user behavior. Specifically, we will compare outcomes by the “high”, “medium”, and “low” risk categories. Additionally, end user activities may vary by potential HRSN, thus we will stratify by specific HRSNs or the number of different HRSNs identified. Additionally, because our prediction models use historical data, we will stratify results by the number of prior encounters in the previous 12 months to explore the potential role of data availability. Finally, we will examine for possible differences by race, ethnicity, sex, and age.

**Alternative strategies**

Alternative strategies may be necessary for defining the sample, applying propensity score matching, and conducting analyses. First, the CDS intervention will be voluntary. If daily access of the CDS (i.e usage) is insufficient for modeling, we will shift from our proposed intention-to-treat analysis for all patients to a per-protocol analysis. In a per-protocol analysis, we could focus on encounters among clinicians who were consistent or more frequent users of Health Dart, based on historical system log data. While this approach could introduce selection bias, making it our secondary strategy, it would offer insights into the CDS intervention's associations and outcomes. We would use the non-adopters from the intervention site as the comparison group and generate propensity score weights for this alternative group. Second, we may not achieve balance in our propensity scores. If that occurs, our first choice will be explore the potential effect of our chosen comparator hospitals. We may be forced to draw our sample from a smaller set of hospitals that better match our intervention site’s practice. Alternatively, we could forego weighting and use individual patient covariates in the model or apply a strict matching approach. Additionally, we could consider including other health systems from the state in our comparison group, although this might impact our ability to measure all study outcomes.

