With a monthly sample of 2,400 at the intervention site, we would have >80% power to detect an odds ratio of 0.75 if the readmission rate in the comparison group was 5.5%. For a readmission rate of 10.5%, we could detect an odds ratio of 0.80 with >80% power. Even if we excluded half of the intervention site patients, our sample size would still be sufficient to detect an odds ratio of 0.70 with 80% power.

1. **Analytic Plan**

We will describe the study sample using proportions and means. Our primary analysis will be a DiD approach comparing patient-encounter outcomes at the CDS intervention site with a propensity score weighted sample from other EDs. As our primary strategy we adopt an intention to treat analysis approach where all eligible encounters at the intervention ED site will be considered as having been exposed to the treatment regardless of actual use of the CDS. The following weighted regression model will estimate the probability of each outcome:

$${Outcome}_{it}=\alpha_{0}+ \beta_{1}{Treat}_{i}+ \gamma{Post}_{t}+ \delta_{rDD}\left( {Treat}_{i}*{Post}_{t} \right)+Z_{it}+\varepsilon_{it}$$

Patient-encounters are indexed by $i$ and time by $t$. ${Outcome}_{it}$ is a binary indicator representing each study outcome. ${Treat}_{i}$ is a binary indicator of inclusion in the CDS intervention group, i.e., patient- encounters at IU Health Methodist ED. ${Post}_{t}$ is a dummy variable indicating all post-intervention go-live months. $\delta_{rDD}$is the DiD estimator and will test our hypotheses that the CDS intervention is associated with each outcome. $Z_{it}$ is a set of patient-level, time varying adjustment covariates. $\varepsilon_{it}$ is the error term. Standard errors will be robust clustered at the highest level feasible; specifically, we will check for clustering at the clinician and patient levels and adjust accordingly. As described above, all observations will be weighted using the propensity score derived weights. We will compare the weighted model with the unweighted model. Given the length of panel, we will also check for, and correct for, autocorrelation as needed.

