**8. Monitoring**

System uptime and end user technical support will be coordinated through the Indiana HIE. The study PI and project manager will review Health Dart usage logs weekly to monitor CDS usage. Follow-up reminder emails containing training materials will be sent monthly. The team will present updates at faculty meetings throughout the study period.

1. **IDP Sharing Statement**

All data generated during the project will be preserved; however, raw and derived data at the patient level will not be publicly posted due to our use of secondary data from privately held electronic health record and health information exchange systems. Because of the data use restrictions established by consortium agreements among the health system partners contributing EHR data to the Indiana Network for Patient Care, patient-level data cannot be shared or disseminated beyond this project. Nevertheless, de-identified derived data at the patient level used in this study may be shared with investigators whose formal requests are approved by the data owners. Requests can be sent to [contact]. Access to this data requires investigator support and a signed data access agreement between the Regenstrief Institute and the investigator’s institution.

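### Low CDS usage would move the analysis from the intention-to-treat difference-in-difference to a same-site adopter comparison, although low usage cannot make the primary model unworkable

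*Protocol*

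**What the plan says.** The Analytic Plan in the protocol fixes the primary contrast: "Our primary analysis will be a DiD approach comparing patient-encounter outcomes at the CDS intervention site with a propensity score weighted sample from other EDs". It also fixes the estimand: "As our primary strategy we adopt an intention to treat analysis approach", under which "all eligible encounters at the intervention ED site will be considered as having been exposed to the treatment regardless of actual use of the CDS". Its regression has a site indicator, a post-period indicator, their interaction (the estimator of interest) and patient-level covariates.

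Alternative strategies then sets a conditional rule. The trigger is "If daily access of the CDS (i.e usage) is insufficient for modeling". The consequence is "we will shift from our proposed intention-to-treat analysis for all patients to a per-protocol analysis". Of the exposed group it says "we could focus on encounters among clinicians who were consistent or more frequent users of Health Dart, based on historical system log data". Of the comparator it says "We would use the non-adopters from the intervention site as the comparison group", with new propensity weights. The same paragraph concedes that selection bias is possible and for that reason ranks the approach second.

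Three other places bear on this. The Intervention section says that use of Health Dart is voluntary. The four hypotheses all concern the effect of implementing the CDS. The pre-specified other outcomes already include, for the intervention site, the share of eligible encounters in which the HRSN page was opened and the share in which Health Dart was opened at all.

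**The concern.** The verb is to shift from one analysis to another, not to add one. One sentence would change three things together: the population (one site instead of the site plus external EDs), the meaning of exposure (a clinician's habits instead of the site and period of care), and the comparator (colleagues in the same department instead of other EDs).

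The stated reason does not fit the model it would replace. Nothing in the ITT regression depends on usage, so sparse usage leaves it as estimable as before.

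At stake is which question the main result answers. For a voluntary tool, poor uptake is one way in which implementation can fail to change care. If the rule is followed, the effect of implementation could go unreported as the primary result in the setting where it is most likely to be small. Its place would be taken by a contrast between clinicians who differ by choice. Screening and referral, the two primary outcomes, are actions on which clinicians' own practice bears directly.

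**Working it through.** **1. Does low usage affect whether the primary model can be fitted?** The terms are Treat, Post, Treat × Post, covariates and error. Treat is 1 for every encounter at the intervention ED. With zero page openings, all four site-by-period cells would still be full and the interaction would still be estimable. The trigger therefore does not describe a failure of this model.

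**2. The plan's own power figure.** The protocol claims more than 80% power for an odds ratio of 0.75 at 5.5% with 2,400 encounters a month, over 9 pre and 9 post months with compound symmetry. Alpha, comparison-group size and the correlation are not stated, so it cannot be reproduced exactly. Assuming two-sided 0.05, equal groups and effective n = 2,400 × 18 / (1 + 17ρ), power is above 99% at ρ = 0.1, 83% at ρ = 0.5 and 66% at ρ = 0.8. The claim is plausible, and the present point does not depend on it.

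**3. What low uptake does to the ITT result (illustration).** From the protocol: baseline 5.5%, odds ratio 0.75, 2,400 a month, 9 months per period, so 9 × 2,400 = 21,600 encounters per cell. Assumed: uptake u, effect only in encounters where the tool is used, independent encounters, equal group sizes, two-sided 0.05.

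- Odds at baseline: 0.055/0.945 = 0.0582. Times 0.75 = 0.04365, a rate of 4.18%. Full-use difference: 1.32 points.
- ITT difference = u × 1.32 points.
- Standard error of the difference-in-difference = √{[3 × 0.055 × 0.945 + p(1 − p)]/21,600}, with p the post-period rate at the site; about 0.30 to 0.31 points.
- Power = Φ(difference/SE − 1.96).

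| Uptake | ITT difference (points) | ITT odds ratio | Power |
|---|---|---|---|
| 100% | 1.32 | 0.75 | 99% |
| 50% | 0.66 | 0.87 | 58% |
| 25% | 0.33 | 0.94 | 19% |
| 10% | 0.13 | 0.975 | 6% |

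The estimate shrinks and power falls, but the model still answers the stated hypothesis.

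**4. What the replacement could show with no CDS effect (illustration).** Assumed: a post-period-only comparison at 5.5%, 25% of the 21,600 encounters from adopters (5,400 against 16,200), and a residual difference d between the two groups' patients.

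- For d = 0.5 points: odds ratio (0.050/0.950)/(0.055/0.945) = 0.90. The pooled rate is 5.375%, the null SE 0.354 points and the alternative SE 0.347 points. The chance of a significant favourable result is Φ[(0.5 − 1.96 × 0.354)/0.347] = 29%, against a nominal 2.5%.
- For d = 0.25 points: odds ratio 0.95, chance 10%.
- For d = 1.0 point: odds ratio 0.81, chance 83%.

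These figures hold only if pre/post differencing is dropped. If it is kept, a fixed difference d cancels, and bias comes only from differing trends or changing case mix. The protocol does not say which applies.

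**5. What the adopter contrast would measure.** Adopters may be defined by past use of the Health Dart platform. The protocol counts platform access and HRSN-page access as separate measures. A frequent platform user need not open the HRSN page, and a non-adopter at the site may open it. The contrast would therefore also be diluted and would not return the effect per page opening.

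**The case against.** The protocol recognises the weakness: it names selection bias, ranks the adopter analysis second and calls ITT primary. It does not say that the ITT result would be withheld. This stands as a mitigating point, but being ranked second, beside a statement that the team will shift, reads as a fallback. It does not say that ITT stays primary.

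A reader might infer that the team could switch after seeing a null result. The documents do not support that. The trigger is usage, and the Monitoring section says only that the team "will review Health Dart usage logs weekly to monitor CDS usage", alongside technical support and reminders. It describes no outcome review and is not linked to the switch. What remains is that uptake is known after go-live and bears on how small the ITT effect will be.

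A reader might also infer that the adopter analysis is bound to exaggerate the benefit by the full standing difference between clinicians. That does not follow either. A fixed difference cancels if the differencing is kept. The propensity covariates for this group are not listed, so it is unknown whether clinician factors enter. Non-adopters can use the same CDS, which would pull the contrast toward the null.

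A numerical usage threshold is the kind of detail that a statistical analysis plan may hold, so its absence here is not part of this point. Poor uptake would also be visible whichever model is used, because the access rates are pre-specified.

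**Conclusion.** The point holds as an inconsistency between the Analytic Plan and Alternative strategies, with a consequence for the primary estimand. The ITT model is defined without regard to use, and the rule for leaving it rests on use. As written, the rule replaces population, exposure and comparator according to post-go-live uptake, and moves to a comparison that the protocol concedes may be biased.

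The size can only be illustrated. At 10% to 25% uptake, under the assumptions above, the ITT odds ratio would be about 0.975 to 0.94 with 6% to 19% power. With no CDS effect and no differencing, a residual difference of 0.5 to 1.0 point would give an odds ratio of 0.90 to 0.81. Uptake, adopter share and residual differences are all assumed. The net direction of bias in the adopter contrast is not determined by the documents. The conclusion does not need these figures: it rests on the model having no usage term and on hypotheses stated in terms of implementation.

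**What to change.** In Alternative strategies, replace the shift with a statement that the ITT difference-in-difference against external comparators remains the primary analysis at any level of usage. Say that it will be read beside the HRSN-page and Health Dart access rates already specified.

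Keep the adopter analysis only as supplementary and exploratory. Retain the pre/post differencing in it, and fix the definition of an adopter in advance.

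If an effect among accessed encounters is wanted, the ITT estimate can be scaled by the access rate. This should be optional and should state its assumption that the intervention acts only through opening the HRSN page. The reminder emails with training materials and the faculty-meeting updates described under Monitoring could make that assumption doubtful.

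The core change is wording only, with no new data and no change to the primary model. The downside is that the headline effect may be diluted or null if uptake is poor. The optional scaling would be a further analysis to specify.

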**8. Monitoring**

System uptime and end user technical support will be coordinated through the Indiana HIE. The study PI and project manager will review Health Dart usage logs weekly to monitor CDS usage. Follow-up reminder emails containing training materials will be sent monthly. The team will present updates at faculty meetings throughout the study period.

1. **IDP Sharing Statement**

All data generated during the project will be preserved; however, raw and derived data at the patient level will not be publicly posted due to our use of secondary data from privately held electronic health record and health information exchange systems. Because of the data use restrictions established by consortium agreements among the health system partners contributing EHR data to the Indiana Network for Patient Care, patient-level data cannot be shared or disseminated beyond this project. Nevertheless, de-identified derived data at the patient level used in this study may be shared with investigators whose formal requests are approved by the data owners. Requests can be sent to [contact]. Access to this data requires investigator support and a signed data access agreement between the Regenstrief Institute and the investigator’s institution.
